#### **12.1.4 Duration of response (DoR)**

DoR is defined as the time from the date of first compliance with response to the date of PD or death due to any cause. The end date of the response should be consistent with the date of the endpoint PFS. The start of DoR is defined as the latest date of the visit at which PR or CR criteria are first met. If a patient does not progress after a response, the censored time for PFS will be used for DoR.

Intracranial duration of response (iDoR) and systemic duration of response (DoR) will be assessed separately.

#### **12.1.5 Disease control rate (DCR)**

DCR is defined as the proportion of patients with the best overall response, which includes CR, PR, or SD.

Intracranial disease control rate (iDCR) and systemic disease control rate (DCR) will be assessed separately.

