#### **9.1.2.2 Treatment visits**

##### **Treatment visits (C1, C2)**

On the first day of the first 2 treatment cycles, treatment period visits will be conducted. The specific visit procedures are as follows:

- Drug dispensing, comprehensive physical examination, body weight measurement, ECOG PS scoring, vital signs measurement, laboratory tests (clinical biochemistry, hematology, and urinalysis), and 12-lead ECG are conducted on C1D1 and C2D1 (Drugs of 1 treatment cycle or 2 treatment cycles are dispensed on C1D1 or C2D1).
- Venous blood sampling: Blood samples should be collected within 7 days pre-administration and post-administration on C1D1 and C2D1.
- Ophthalmological examinations will be performed as clinically indicated throughout the treatment period, and the examination items will be determined by the investigator based on the subject's condition
- Echocardiography will be performed when clinically indicated
- Response evaluation in solid tumors will be performed as per RECIST 1.1 on C2D1: Tumor assessment will include enhanced CT (preferred) or enhanced MRI of the chest and abdomen (including liver and adrenal glands), enhanced MRI (preferred)/enhanced CT of the head, and the sites of positive lesions (enhanced CT/enhanced MRI) confirmed at baseline. The imaging method should be consistent with that at baseline whenever feasible (unless there are contraindications or force majeure factors)
- AEs and concomitant medications will be recorded

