## 12.0 ENDPOINT EVALUATION AND STATISTICAL ANALYSIS

### 12.1 Anti-Tumor Activity Evaluation

#### 12.1.1 Investigator assessment as per RECIST 1.1

At each visit, the investigator will assess the patient's tumor response to treatment as CR, PR, SD, or PD as per RECIST 1.1 by comparing with baseline and previous assessments, depending on patient's status. The progression of TLs will be calculated by comparing with tumor burden at its nadir (i.e., the smallest sum of previously recorded diameters). In the absence of progression, tumor response (CR and PR) and stable disease (SD) will be calculated by

comparing with baseline tumor measurements obtained prior to the start of the treatment. For patients with indeterminable tumor status, if there is evidence of progression, they will be considered to have PD; if there is no evidence of progression, they will be considered inevaluable (NE). The endpoints of this study will be analyzed based on the tumor response assessment by the investigator per RECIST 1.1, and the investigator will also manage subjects only based on the assessment results.

The investigator will evaluate patient's response to treatment using RECIST 1.1 (see Appendix D) by determining the objective response rate (ORR), disease control rate (DCR), duration of response (DOR), and progression-free survival (PFS). In addition to the overall tumor imaging evaluation performed by the investigator as per RECIST 1.1, for systemic and/or intracranial lesions (no more than 5 target lesions in the whole body) selected for overall evaluation, the respective intracranial and systemic response evaluation (intracranial: iPFS, iORR, iDCR, and iDoR; systemic: PFS, ORR, DCR, and DoR) will be performed according to the response evaluation criteria in RECIST 1.1, and the investigator does not need to select additional lesions.

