| Comments                             | 
a. Subjects will be followed up at Week 4, Week 12, and every 8 weeks thereafter, and the efficacy should be confirmed as soon as possible for patients with PR/CR at Week 4.
 
b. Subjects should complete the visit procedures within 28 days (+7 days) after discontinuation of IMP, and ongoing and new AEs should be followed up. All AEs should be followed up until recovery or returning to the baseline level, or loss to follow-up or death of the subject. After the end of the safety follow-up period, only SAEs considered related to aumolertinib or study procedures will be collected.
 
c. A cycle is defined as 28 consecutive days of treatment.
 
d. At baseline, this evaluation should be completed before administration on the visit day. If the screening examinations are completed within 7 days before the first dose of the IMP, they can be exempted on C1D1.
 
e. Venous blood sampling: Blood samples will be collected at the following points: within <math>\pm 7</math> days before C1D1 and C2D1 administration, and within 1 week after PD (24 h after the previous dose).
 
f. Tumor tissue slice collection: 10–15 histopathological slices need to be collected before C1D1 administration and within one week after PD (24 h after the previous dose)
 
g. An ECG will be performed at the time of any cardiac-related AE.
 
h. Baseline examinations should be performed within 28 days prior to the first dose. After the start of treatment, subjects will be evaluated once every 8 weeks until PD is confirmed as per RECIST 1.1, even if the subjects discontinue the treatment or receive other anti-tumor treatments before PD. Tumor assessment data will be obtained from CT or MRI (contrast-enhanced CT or MRI is recommended as the preferred method).
 |  |  |  |  |  |                                                     |   |

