**Table 2. Overall response of target lesions**

|                                 |                                                                                                                                                                                                                                                                                            |
|---------------------------------|--------------------------------------------------------------------------------------------------------------------------------------------------------------------------------------------------------------------------------------------------------------------------------------------|
| Complete response (CR)   | Disappearance of all target lesions from baseline. Any pathological lymph nodes selected as TLs must have a short axis of $< 10$ mm.                                                                                                                                                       |
| Partial response (PR)    | At least a 30% decrease in the sum of diameters of TLs, taking as reference the baseline sum diameters.                                                                                                                                                                                    |
| Stable disease (SD)      | Neither sufficient shrinkage to qualify for PR nor sufficient increase to qualify for PD.                                                                                                                                                                                                  |
| Progressive disease (PD) | At least a 20% increase in the sum of diameters of TLs, taking as reference the smallest sum on study (this includes the baseline sum if that is the smallest on study). In addition to the relative increase of 20%, the sum must also demonstrate an absolute increase of at least 5 mm. |
| Inevaluable (NE)         | Only relevant TLs are not assessed or not evaluable or have lesion intervention.
Note: If the sum of diameters meets the criteria of PD, the lesion is not inevaluable and should be classified as a PD.                                                                                |

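### DCR and iDCR count SD with no minimum time on study, so one SD reading as early as Day 22 can count as disease control

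*Protocol*

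**What the plan says.** **Endpoint rule.** Section 12.1.5 says: "DCR is defined as the proportion of patients with the best overall response, which includes CR, PR, or SD". It adds: "Intracranial disease control rate (iDCR) and systemic disease control rate (DCR) will be assessed separately". Both are named secondary endpoints (Section 5.2.1), each to be reported as a percentage with a 95% CI.

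**What SD means.** Appendix D, Table 2 defines it by size alone: "Neither sufficient shrinkage to qualify for PR nor sufficient increase to qualify for PD". Section 12.1.1 fixes only the reference measurement: "In the absence of progression, tumor response (CR and PR) and stable disease (SD) will be calculated by" comparison with the pre-treatment scan. Appendix D, Table 4, which derives the overall response, has no time element, and Section 10.2.1 adds none.

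**When scans happen.** Section 9.1.2.2: "Response evaluation in solid tumors will be performed as per RECIST 1.1 on C2D1". Appendix B, comment c: "A cycle is defined as 28 consecutive days of treatment". Its schedule table places C2D1 at Day 29 with a 7-day window either side. Comment a gives the sequence: "Subjects will be followed up at Week 4, Week 12, and every 8 weeks thereafter". The same comment says "the efficacy should be confirmed as soon as possible for patients with PR/CR at Week 4", and no such instruction exists for SD.

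**Competing schedules.** Section 10.2.1 (like the synopsis and Section 6.1) gives assessment every 8 weeks, with a 1-week window. Appendix D, Section 4.1 gives every 6 weeks ± 7 days.

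**The concern.** SD is the category that separates DCR from ORR. Early in treatment, most tumours that will soon progress have not yet grown enough to be called PD. Without a time floor, an early scan can therefore give a patient a best response of SD that no later scan supports, and best response is never revised downward.

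Two things are at stake. First, part of what is reported as disease control would be a single reading about three to four weeks into treatment. Second, the same disease course can be classified differently according to which of the protocol's schedules is followed, and about 20 sites are planned. A patient stable at Week 4 who progresses before Week 8 is controlled if scanned at Week 4, and has PD as best response if first scanned at Week 8.

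**Working it through.** **1. Calendar check**, with first dose on Day 1 and 28-day cycles.

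- C2D1 = 28 + 1 = Day 29, which reproduces the Appendix B figure. Window: 29 − 7 = Day 22 to 29 + 7 = Day 36.
- Next scan, C4D1 (Week 12) = 3 × 28 + 1 = Day 85, also as in Appendix B. Window: Day 78 to Day 92. (Section 9.1.2.2 heads that visit block D113+, but 4 × 28 + 1 = 113 is C5D1. This too needs reconciling and would only put the next scan later.)
- 8-weekly text read as a first scan at Week 8: Day 57 − 7 = Day 50.
- 6-weekly text: Day 43 − 7 = Day 36.

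| Schedule | Earliest SD that counts |
|---|---|
| Section 9.1.2.2 and Appendix B (Week 4, Week 12) | Day 22 |
| Appendix D, 4.1 (every 6 weeks) | Day 36 |
| Section 10.2.1 (every 8 weeks) | Day 50 |

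**2. Apply the rule.** A patient has SD on Day 22 and PD on Day 85. Under Appendix D, Table 4 the two visit responses are SD and PD. The better is SD, so Section 12.1.5 counts the patient in DCR, or in iDCR if the readings are intracranial.

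**3. How many patients could be concerned?** The protocol gives no early progression rate. I assume exponential PFS through its 12-month rates of 40% and 60% (Section 5.3) and the planned 63 patients:

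S(d) = p^((d − 1)/365.25), where p is the 12-month rate and d the study day.

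| | p = 0.60 | p = 0.40 |
|---|---|---|
| S(Day 29) | 0.9616 | 0.9322 |
| S(Day 57) | 0.9247 | 0.8690 |
| S(Day 85) | 0.8892 | 0.8100 |
| Event between Weeks 4 and 8 | 3.7% (63 × 0.0369 = 2.3) | 6.3% (63 × 0.0632 = 4.0) |
| Event between Weeks 4 and 12 | 7.2% (63 × 0.0724 = 4.6) | 12.2% (63 × 0.1222 = 7.7) |

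Across the visit windows (Day 36 to 78 at the narrowest, Day 22 to 92 at the widest), the Week 4 to Week 12 share runs from 5.4% to 9.1% at p = 0.60 and from 9.2% to 15.3% at p = 0.40.

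**4. Reading the table.** The Week 4 to 8 row is the group whose classification differs between the Week 4 and the 8-weekly schedules. The Week 4 to 12 row is the wider group with an event by the Week 12 scan. At the nominal visit days both are upper bounds on the patients with SD and then PD: those with CR or PR at Week 4 count as controlled anyway, and some events are deaths. For iDCR the relevant curve is iPFS, for which the protocol makes no assumption.

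**The case against.** **A minimum SD interval is a derivation detail that a SAP often supplies.** True in general. Here, however, the protocol states the rule itself and sets out the response algorithm in Appendix D, and what it states counts an isolated early SD.

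**Day 22 rests on one side of a schedule conflict.** This stands. If the first scan is at Week 8, the earliest SD is Day 50, which is 49 days or 7 weeks after first dose, and the early-scan problem disappears. But Section 9.1.2.2 and Appendix B do call for the C2D1 scan, and no schedule comes with a written floor.

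**The size is easily overstated.** This also stands. A reader might take 7 to 12 points as the inflation of DCR. Only 3.7 to 6.3 of those points fall before Week 8. The remaining 3.5 to 5.9 points are patients still event-free at Week 8, whom an 8-weekly schedule could count as controlled.

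**Stronger inferences the documents do not support:**

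- That DCR would sit near its ceiling whatever the drug does. The Week 4 progression-free share still differs, 93.2% against 96.2%.
- That any scan without PD suffices. An inevaluable scan (NE) is not SD and does not count.
- That a comparison with the background figures (DCR 93.4%, CNS DCR 91.3%) would be biased. No such comparison is planned, and the protocol does not say how SD was defined for those figures.

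**The endpoints are descriptive, and early progression shows in PFS and iPFS.** Correct. This limits the importance of the point but does not make the DCR rule sound.

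**Conclusion.** The point holds in limited form. As written, Section 12.1.5 counts a single SD reading from Day 22 onward as disease control even when the next scan shows PD, and the earliest qualifying day moves from Day 22 to Day 50 according to which schedule is followed. That much rests on the text and calendar arithmetic alone.

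The size is illustrative and rests on an exponential curve through the protocol's own 12-month rates: at most about 2 to 4 of 63 patients with events between Weeks 4 and 8, and about 5 to 8 between Weeks 4 and 12. No size can be given for iDCR. The consequence is confined to two descriptive secondary endpoints; the primary endpoint and the sample size are untouched. It is worth correcting before results are known because the correction uses data already collected.

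**What to change.** 1. Reconcile the assessment schedules: Week 4 then Week 12 (Section 9.1.2.2, Appendix B), every 8 weeks (Section 10.2.1), and every 6 weeks (Appendix D, 4.1).

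2. Add to Section 12.1.5, for DCR and iDCR alike: SD (or Non-CR/Non-PD) counts only if an evaluable assessment without PD is documented at least 7 weeks after first dose, that is, 8 weeks less the 1-week window. Earlier SD followed by PD has best response PD. Earlier SD with no further assessment is NE and is counted as not controlled.

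The floor should attach to the date of a documented scan. If SD duration were instead counted from first dose to the PD date, PD on Day 78 to 92 would still pass a 6- or 8-week minimum and nothing would change.

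**Cost.** No new data or visits. Reported DCR and iDCR would be expected to be a few points lower, and patients with early SD and no later scan, who are not in the figures above, would also move to not controlled. If the Week 4/Week 12 schedule is kept, no scan is due between Day 36 and Day 78, so the floor in effect requires the Week 12 scan, and a patient who progresses between Weeks 8 and 12 is counted as not controlled. If the 6-weekly schedule is kept, its first window (Day 36 to 50) reaches the floor only on its last day, with much the same effect. The 7-week figure should therefore be set together with the reconciled schedule, and this downside stated.

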#### **12.1.6 Overall survival (OS)**

OS is defined as the time from the date of the first dose to the date of the patient's death due to any cause. A patient who has not died at the time of statistical analysis will be censored at the time point when the patient is last known to be alive.

### **12.2 Safety Evaluation**

All safety data will be summarized at the end of the study. All data from the initiation of treatment until 28 days after the last dose will be summarized together in the safety evaluation. Data prior to initiation of treatment will be summarized but not included in the summary table of AEs.

### **12.4 Statistical Analysis Methods**

#### **12.4.1 Definitions of statistical analysis sets**

- **Full analysis set (FAS)**

The FAS is defined as all patients with at least one dose of the study drug.

- **CNS evaluable-for-response set (cEFR)**

The cEFR is defined as a subset of the FAS and includes patients who have at least one measurable brain lesion. Baseline and demographic characteristics will be analyzed in the FAS and cEFR, and the efficacy evaluation will be performed in both the FAS and the cEFR. The results will be mainly based on the FAS.

- **Safety set (SS)**

The SS is defined as all patients who have received at least one dose of the study treatment. Safety evaluation will be based on the SS.

#### **12.4.2 Efficacy analysis**

Efficacy endpoints will be analyzed using results evaluated by the investigator as per RECIST 1.1.

##### **12.4.2.1 Analysis of primary efficacy endpoint (12-month PFS rate)**

The Kaplan-Meier plot will be generated, and the 12-month PFS rate, median PFS and its 95% CI will be calculated. In addition, the PFS rate at 6, 12, 18, and 24 months will be summarized.

##### **12.3.2.2 Analysis of secondary efficacy endpoints**

- **iPFS**

The Kaplan-Meier plot will be generated, and the median iPFS and its 95% CI will be calculated. In addition, the iPFS rate at 6, 12, 18, and 24 months will be summarized.

- **OS**

The Kaplan-Meier plot will be generated, and the median OS and its 95% CI will be calculated. In addition, the OS rate at 6, 12, 18, and 24 months will be summarized.

- **ORR (including systemic and intracranial ORR)**

ORR will be summarized as percentage, and its 95% CI will be calculated.

- **DoR (including systemic and intracranial DoR)**

The Kaplan-Meier plots will be generated, and the median DoR and 95% CI will be calculated.

- **Analysis of DCR (including systemic and intracranial DCR)**

DCR will be summarized as percentage, and its 95% CI will be calculated.

#### **12.4.3 Safety analysis**

##### **12.4.3.1 Adverse events**

The AEs that occur from the initiation of treatment until 28 days after the last dose will be summarized in the safety evaluation. The AEs that occur prior to initiation of treatment and AEs that occur after 28 days following the last dose will be tabulated separately and not included in the summary table of AEs.

Treatment-emergent AEs will be summarized by treatment group, mainly including:

- 1) Number and proportion of patients with at least one AE;
- 2) Number and proportion of patients with at least one treatment-related AE;
- 3) Number and proportion of patients with at least one severe (CTCAE Grade  $\geq 3$ ) AE;
- 4) Number and proportion of patients with at least one severe (CTCAE Grade  $\geq 3$ ) treatment-related AE;
- 5) Number and proportion of patients with at least one SAE;
- 6) Number and proportion of patients with AEs resulting in dose modification;
- 7) Number and proportion of patients with AEs resulting in withdrawal;
- 8) Number and proportion of patients with AEs resulting in death.

All AEs will be summarized by SOC and PT. All AEs will be tabulated.

##### **12.3.3.2 Laboratory tests**

For the laboratory test values which are measurement data (such as body weight, vital signs, hematology, urinalysis, and blood biochemistry), the baseline, post-dose, and post-dose change data will be summarized by each follow-up visit and treatment group; for qualitative data (such as normal/abnormal and clinically significant/insignificant test results), the changes from baseline to each post-dose follow-up will be summarized in a list.

##### **12.3.3.3 ECG analysis**

The mean  $\pm$  standard deviation, maximum, minimum, and median will be used to describe the measured values and changes in heart rate, PR interval, QT interval, and QTcF interval before and after treatment. According to the normal and abnormal findings judged by the investigator, the normal and abnormal changes before and after treatment will be described.

Abnormal QTcF interval at baseline and after treatment will be described by the proportion of QTcF interval change from baseline of  $\leq 30$  ms, 30–60 ms, and  $> 60$  ms after treatment (maximum), and the proportion of QTcF interval change from baseline of  $\leq 30$  ms, 30–60 ms, and  $> 60$  ms after treatment.

##### **12.3.3.4 Ophthalmological examination**

For qualitative data for the ophthalmological examination (such as normal/abnormal and clinically significant/insignificant test results), changes from baseline to each follow-up post-dose will be summarized in a list.

##### **12.3.3.5 ECOG PS score**

Changes in the ECOG PS score from baseline to each follow-up post-dose will be summarized in a cross-tabulation.

#### **12.4.4 Pharmacokinetic analysis**

The pharmacokinetics of aumolertinib and its metabolite HAS-719 will be characterized, including the cerebrospinal fluid concentrations of aumolertinib and its metabolite HAS-719.

### **13.0 DATA PROCESSING AND RETENTION**

Full details of data processing procedures will be documented in a separate data management plan.

#### **13.1 Electronic Case Report Form**

Each patient who signed the informed consent form will be required to complete the eCRF.

The sponsor or designated personnel will provide the study sites with access to the eCRFs. Training will be provided by the funder to the personnel using the eCRFs. Information to be collected in this study using eCRFs will be transmitted to the sponsor, the funder, and regulatory authorities. The data will be entered directly into the eCRFs.

All amendments should be recorded, including the old information, the new information, the person making the amendment, the date of the amendment, and the reason for the change. In addition, the reasons for major amendments should be included.

The principal investigator must review the eCRFs for integrity and accuracy and must sign and date the eCRFs.

Besides, the investigators must retain full responsibility for the accuracy and authenticity of all data entered into the eCRFs.

The eCRFs will be reviewed for integrity and accuracy during periodic visits by the authorized CRA. The sponsor or designated personnel will be permitted to review patients' medical and hospital records pertinent to the study to ensure the accuracy of the eCRFs. All eCRF data are owned by the sponsor and the funder. Unless written permission is obtained from the sponsor and the funder, the data shall not be provided to any third party in any form, except to authorized representatives of the relevant government regulatory authorities.

